#### Sample size

2.1.2

The sample size estimation for this study was calculated based on the results of a pilot study by Cairns (2018). This pilot study was selected as a reference for several reasons: both studies involve similar populations (family members of ICU patients), comparable intervention intensity (continuous intervention over 3 days, each lasting 15–20 min), similar assessment tools and outcome indicators (key indicators in this study were selected from those that performed well in the Cairns’ study, or alternative validated tools were chosen to address its limitations), and largely aligned assessment time points (the Cairns’ study assessed on Day 1, Day 3, Day 30, and Day 90; this study additionally included an assessment within 24 h after patient discharge to better reflect the interaction between patients and their families). In the pilot study (*N* = 10; 5 per group), the effect size for the outcome of perceived stress from baseline to 90-day follow-up was Cohen’s *d* = 1.13 (95% CI: −0.21 to 2.47), based on a mean difference of 4.4 points (intervention: 23.0 ± 2.30 vs. control: 25.0 ± 5.05). This effect size represented the most conservative estimate among all follow-up time points (Day 3: *d* = 1.50; Day 30: *d* = 1.23; Day 90: *d* = 1.13). Sample size estimation for the “independent sample *t*-test” was performed in G Power3.1 sample size calculation software,^1^ and the calculation formula is as follows: 
$n={\left[\frac{Z_{\alpha /2}+Z_{\beta }}{\delta /\sigma }\right]}^{2}(Q_{1}^{-1}+Q_{2}^{-1})$
 (Faul et al., 2007; Faul et al., 2009). The parameter Settings are as follows: For the two-sided test, Cohen’s d is 1.13, Alpha is 0.05, the certainty Power (1-β) is 0.95, and the sample size is selected as N1 = N2. Finally, it was calculated that each group of the intervention study required 22 people. Considering a loss to follow-up rate of more than 20%, the minimum sample size included in each group was ultimately 28 people. When the sample size was sufficient, as many research subjects as possible were included in the study. Acknowledging the inherent variability and potential overestimation in pilot studies, we aimed for a conservative design by selecting a high statistical power to minimize the risk of Type *II* error.

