To account for the inherent uncertainty in the pilot-derived effect size estimate, we conducted a sensitivity analysis using a range of more conservative effect sizes. The results are shown in Table 1. With 28 participants per group, our trial maintains 80% power to detect a medium-to-large effect (*d* = 0.7), which we consider a clinically meaningful target.

**Table 1 tab1:** Sensitivity analysis of sample size under different effect size scenarios.

Scenario	Effect size (d)	Power	Required N per group	Our *N* = 28 achieved power
Pilot estimate (Day 90)	1.13	0.95	20	>99%
Large effect	0.80	0.95	36	88%
Medium-large effect	0.70	0.95	46	80%
Medium effect	0.50	0.80	64	51%
Lower bound of 95% CI	0.21	0.80	358	12%

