### Statistical analysis

2.6

In this study, EpiData3.1 software will be utilized for data entry, while IBM SPSS Statistics version 27.0 will be employed for data analysis.

All statistical tests were two-sided with *α* = 0.05, and *p* < 0.05 indicated significance. Categorical variables, including family member demographics, will be presented as counts and percentages and compared between groups using the *chi-square* test or *Fisher’s* exact test, as appropriate. Continuous variables will be assessed for normality using the *Shapiro–Wilk* test. Normally distributed data will be summarized as mean ± standard deviation, while non-normally distributed data will be summarized as median and interquartile range. For baseline comparisons of continuous variables, independent samples *t*-tests or *Mann–Whitney U* tests will be applied accordingly. For the intention-to-treat (ITT) analysis, missing data from participants who withdraw during the study will be handled using multiple imputation (MI). Specifically, the multiple imputation module in SPSS version 27.0 will be employed to create five complete datasets using the fully conditional specification method, with group allocation, time point, baseline scores, and demographic characteristics included as predictor variables. The imputed results will then be pooled for analysis.

Primary Outcome Analysis: The primary analysis will follow the ITT principle, including all randomized participants. The efficacy of the SAF-T intervention will be assessed by comparing the psychological distress composite score at the primary endpoint (Day 3) between the intervention and control groups, adjusting for the baseline composite score. (1) Calculation of the composite score. To ensure comparability across time points, all composite scores will be standardized using the means and standard deviations calculated from the Day 3 assessments. For each participant at Day 3, the composite score will be calculated as follows: First, for each of the three scales (PSS-10, GAD-7, and PHQ-9) administered at Day 3, the mean (
${\overset{ˉ}{x}}_{k}$
) and standard deviation (
$SD_{k}$
) will be calculated across all participants, where 
k=1,2,3
 represents the three scales, respectively. Second, for each participant 
i
, the raw score on each scale (
$x_{\mathrm{ik}}$
) will be standardized to a Z-score: 
$Z_{\mathrm{ik}}=\frac{x_{\mathrm{ik}}-{\overset{-}{x}}_{k}}{SD_{k}}$

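### Table 1 does not follow from the stated t-test: 28 per group gives 73% power at d = 0.7, not 80%, and several other cells are wrong

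*Protocol article*

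**What the plan says.** Section 2.1.2 of the protocol article sizes the trial for an independent-samples t-test; the calculation "was performed in G Power3.1 sample size calculation software". The inputs are a two-sided test, d = 1.13, equal groups, and "Alpha is 0.05, the certainty Power (1-β) is 0.95". The result is that "each group of the intervention study required 22 people", raised to 28 to allow for a loss to follow-up above 20%. Section 2.6 confirms the sidedness: "All statistical tests were two-sided with" alpha 0.05.

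A sensitivity analysis follows, offered because the pilot effect size is uncertain. Its conclusion is "With 28 participants per group, our trial maintains 80% power to detect a medium-to-large effect", with d = 0.7 described as a clinically meaningful target. Table 1 lists, for d = 1.13, 0.80, 0.70, 0.50 and 0.21:

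- required N per group of 20, 36, 46 (at 95% power), 64 and 358 (at 80% power);
- power at 28 per group of >99%, 88%, 80%, 51% and 12%.

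The last row is labelled "Lower bound of 95% CI" with d = 0.21, while the text reports the pilot interval as "95% CI: −0.21 to 2.47".

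**The concern.** Two conflicts can be seen without calculation. For the same d = 1.13 and 95% power, the text requires 22 per group and the table 20. The lower confidence bound is negative in the text and positive in the table.

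The larger matter is the 80% figure. The table is the protocol's safeguard against relying on a 10-person pilot, and d = 0.7 is the effect the protocol says it wants to be able to detect. If power there is overstated, a null result could be read as evidence against a meaningful effect from an adequately powered trial, when the risk of missing that effect is 27% rather than 20%. The power errors at d = 0.50, 0.70 and 0.80 all run in the trial's favour.

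**Working it through.** **Inputs** (sections 2.1.2 and 2.6): two-sided alpha 0.05; independent-samples t-test; equal groups; n = 28 per group; effect sizes and target powers as in Table 1.

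**Formulas.** Exact power uses the noncentral t distribution with 2n − 2 degrees of freedom and noncentrality d × √(n/2). Required n is the smallest integer that reaches the target power. As a cross-check, the printed normal formula with equal groups reduces to n per group = 2(z₁ + z₂)²/d².

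**Step 1: the base calculation reproduces.** At d = 1.13 and 95% power, 21 per group gives 94.7% and 22 gives 95.6%, so 22 are required. Then 22/0.8 = 27.5, rounded up to 28. This matches the text and confirms the method. Table 1's 20 per group gives 93.6%.

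**Step 2: the 80% claim.** At d = 0.7 and n = 28, the noncentrality is 0.7 × √14 = 2.619, with 54 degrees of freedom and critical value 2.005. Power is 73.0%. The normal approximation gives Φ(2.619 − 1.960) = Φ(0.659) = 74.5%. Exactly 80% needs 34 per group (33 gives 79.97%). With 28 per group, the effect detectable at 80% power is d = 0.76.

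**Step 3: the whole table, exact t (normal approximation in brackets).**

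| d | Target power | Required N, printed | Required N, recomputed | Power at 28, printed | Power at 28, recomputed |
|---|---|---|---|---|---|
| 1.13 | 0.95 | 20 | 22 (21) | >99% | 98.6% (98.8%) |
| 0.80 | 0.95 | 36 | 42 (41) | 88% | 83.6% (84.9%) |
| 0.70 | 0.95 | 46 | 55 (54) | 80% | 73.0% (74.5%) |
| 0.50 | 0.80 | 64 | 64 (63) | 51% | 45.1% (46.5%) |
| 0.21 | 0.80 | 358 | 357 (356) | 12% | 12.1% (12.0%) |

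The printed 36 and 46 give 91.7% and 91.3% power, not 95%.

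**Step 4: could another method explain the table?**

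- One-sided testing gives N of 35 and 45 for d = 0.80 and 0.70, close to the printed 36 and 46. But power at 28 would be 90.5%, 82.7% and 58.0% for d = 0.80, 0.70 and 0.50, and N in the last two rows would be 51 and 282. It also contradicts the stated two-sided test.
- ANCOVA with an assumed baseline to Day 3 correlation of 0.39 multiplies d by 1/√(1 − 0.39²) = 1.086. Power at 28 becomes 99.5%, 89.1%, 79.7%, 51.4% and 13.3%, and N for the 95% rows becomes 19, 36 and 46. Both are close to print, but N in the last two rows would be 55 and 303 against 64 and 358.

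The power column and the 95% rows therefore look adjusted, while the last two N values fit only the unadjusted two-sided test. No single method gives the whole table.

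**Step 5: loss before the primary endpoint.** If 20% were lost by Day 3, 28 × 0.8 = 22.4, or about 22 per group. Power at d = 0.7 is then 62.1%, and the effect detectable at 80% power is about d = 0.86.

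**The case against.** The strongest defence is that the planned primary test is a baseline-adjusted ANCOVA, which is more efficient than the t-test. With a correlation of about 0.4, 28 per group does reach 80% at d = 0.7. That stands as far as it goes: a reader should not infer that the trial cannot have 80% power at d = 0.7, only that the claim is unsupported as written. The article names a t-test for sizing, gives no correlation, and prints two rows that fit only the unadjusted test. With a correlation of 0.39 and 22 per group, power would be about 69%.

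Second, N = 56 does not rest on Table 1. This is correct: the base calculation at d = 1.13 reproduces, and correcting the table leaves it untouched.

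Third, a reader might take 62% as the trial's expected power. The documents do not support that. The 20% is a general loss to follow-up rate, the limitations section ties attrition to the 90-day follow-up, and the primary endpoint is Day 3. The sentence is also openly conditional on 28 per group. The 62% is what follows if the whole loss occurs by Day 3.

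Fourth, a reader might infer that no sample size can be computed for a bound of −0.21. That is not so: a two-sided calculation depends on the absolute value of d, and 0.21 gives 357. The fault is the sign and the label. Nor does the row conceal the interval, since the text just before it prints the negative bound.

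Finally, not every cell is wrong. The 64 and 12% reproduce, 358 against 357 is trivial, and so is >99% against 98.6%.

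**Conclusion.** Wrong as written. Under the stated method, power at d = 0.7 with 28 evaluable per group is 73.0% against 80% claimed. The other material errors are required N at d = 0.80 and 0.70 (6 and 9 per group too few), power at d = 0.80 and 0.50 (about 4 and 6 percentage points too high), the 20 against 22 conflict at d = 1.13, and the sign of the confidence bound, which lies on the harm side of zero.

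Allowing for loss, unadjusted power at d = 0.7 lies between 62% and 73%, depending on how much of a loss of up to 20% falls before Day 3. These figures assume the two-sided t-test that the article names. Credit for baseline adjustment would raise them by an amount that depends on a correlation the article does not give. The point concerns stated power; it does not invalidate the calculation behind N = 56.

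**What to change.** Recompute every row of Table 1 by the stated t-test: required N per group of 22, 42, 55, 64 and 357, and power at 28 of 98.6%, 83.6%, 73.0%, 45.1% and 12.1%. Alternatively, state one assumed baseline to Day 3 correlation, with its basis, and apply ANCOVA to all five rows.

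If the t-test is kept, replace the 80% sentence with: 73% power at d = 0.7, and 80% power at d of about 0.76, with 28 evaluable per group. Add that if the full 20% loss occurred by Day 3 (22 per group), power at d = 0.7 would be about 62% and the effect detectable at 80% power about d = 0.86.

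Relabel the 0.21 row as a small-effect scenario or delete it, and say that the pilot interval includes no effect and harm.

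The cost is a correction to text and one table. Sample size, conduct and analysis do not change; the stated power becomes less favourable.

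### Table 1 overstates power: on the stated two-sided t-test, 28 per group gives 73% at d = 0.7, not 80%

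*Protocol article*

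**What the plan says.** Section 2.1.2 (Sample size) fixes the basis of the calculation: "Sample size estimation for the “independent sample *t*-test” was performed in G Power3.1 sample size calculation software". The settings are: "For the two-sided test, Cohen’s d is 1.13, Alpha is 0.05, the certainty Power (1-β) is 0.95", with both arms of equal size. The result is that "each group of the intervention study required 22 people", and the number is then raised for attrition: "Considering a loss to follow-up rate of more than 20%, the minimum sample size included in each group was ultimately 28 people".

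The section accepts that the pilot effect is uncertain and adds a sensitivity analysis, Table 1. Its last column gives achieved power at 28 per group as >99%, 88%, 80%, 51% and 12% for d = 1.13, 0.80, 0.70, 0.50 and 0.21. The text repeats the middle value: "With 28 participants per group, our trial maintains 80% power to detect a medium-to-large effect", with d = 0.7 described as the clinically meaningful target.

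Section 2.6 confirms that all tests are two-sided at 0.05. It analyses the primary outcome by ANCOVA with the baseline composite score as covariate. No baseline to Day 3 correlation appears in the article.

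**The concern.** The test, sidedness, alpha, allocation and group size are all given, so each achieved-power cell can be recomputed. A two-sided t-test with 28 per group falls visibly short of 80% power at d = 0.7.

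The number 56 itself comes from the pilot effect of d = 1.13. That pilot had 10 participants and a 95% confidence interval from −0.21 to 2.47. The 80% sentence is what tells the reader that 56 is still adequate if the true effect is smaller. If it is wrong, the trial misses the usual 80% for its own target on its own stated method, and a null result could be taken as stronger evidence against an effect of that size than the design supports.

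**Working it through.** **Inputs** (all from section 2.1.2): independent-samples t-test, two-sided, alpha 0.05, equal groups, n = 28 per group, and d as listed in Table 1.

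**Formula** (non-central t, the exact power for this test):
- degrees of freedom = 2n − 2
- non-centrality λ = d × √(n/2)
- power = P(|T| > t_crit), where T is non-central t with that df and λ

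**The plan's own figure first.** At d = 1.13, n = 22 gives df = 42, λ = 1.13 × √11 = 3.748 and power 95.6%; n = 21 gives 94.7%. So 22 is the smallest n reaching 95%, as the text says. Then 22/(1 − 0.20) = 27.5, rounded up to 28. The method therefore matches the one used for the main calculation.

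**Achieved power at n = 28.** Here df = 54, t_crit = 2.005 and √(28/2) = 3.742.

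| d | λ | Two-sided t | Printed | Normal approx. | One-sided t |
|---|---|---|---|---|---|
| 1.13 | 4.228 | 98.6% | >99% | 98.8% | 99.4% |
| 0.80 | 2.993 | 83.6% | 88% | 84.9% | 90.5% |
| 0.70 | 2.619 | 73.0% | 80% | 74.5% | 82.7% |
| 0.50 | 1.871 | 45.1% | 51% | 46.5% | 58.0% |
| 0.21 | 0.786 | 12.1% | 12% | 12.0% | 19.2% |

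The printed values at d = 0.80, 0.70 and 0.50 lie between the two-sided and one-sided results and match neither. The overstatement is about 4, 7 and 6 points. At d = 1.13 it is under half a point, and at d = 0.21 there is none.

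**What 28 per group does give.** Solving for 80% power at n = 28 gives d = 0.76. At d = 0.7, n = 33 gives 79.97% and n = 34 gives 81.2%, so 80% needs 34 per group.

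**Could baseline adjustment explain the column?** With an assumed baseline to Day 3 correlation ρ, ANCOVA replaces d by d/√(1 − ρ²) and df by 53. At d = 0.7:

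| Assumed ρ | Adjusted d | Power |
|---|---|---|
| 0.3 | 0.734 | 76.9% |
| 0.4 | 0.764 | 80.1% |
| 0.5 | 0.808 | 84.4% |
| 0.6 | 0.875 | 89.5% |

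At ρ = 0.38 the whole column would be 99.4%, 88.8%, 79.4%, 51.0% and 13.3%, which is close to print except at d = 0.21. But the same ρ would make the required n 55 at d = 0.50 and 306 at d = 0.21. Table 1 prints 64 and 358. The unadjusted two-sided t-test gives 64 and 357.

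**The case against.** The strongest reply is that the t-test is only the planning basis. The primary analysis is an ANCOVA, and with a baseline correlation of about 0.4 the trial would have 80% power at d = 0.7 after all. This stands as far as it goes: the 27% type II risk belongs to the t-test, and the true power of the adjusted analysis may be higher. It does not support the printed figure, because the section names an unadjusted t-test, gives no correlation, and prints cells in the same table that fit zero correlation.

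Those matching cells do not prove what was intended. The required n of 20, 36 and 46 in the 95% power rows fit neither the unadjusted two-sided t-test (22, 42 and 55) nor the 22 in the text. That is a separate error, and it shows that Table 1 has no single basis.

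It can also be said that 56 was derived from d = 1.13 and that this derivation reproduces, so correcting Table 1 changes no recruitment number. That is right. The sentence is still the section's only quantitative reassurance about effects smaller than the pilot's. How readers would treat a null result is a judgement, since the article does not commit to interpreting one through this table. Finally, the error at d = 1.13 is immaterial on its own.

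**Conclusion.** The concern holds. On the stated basis, the 80% claimed for d = 0.7 should be 73%, and the 88% and 51% cells should be 84% and 45%. The >99% cell is marginally high and the 12% cell is correct.

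These figures assume a two-sided t-test at alpha 0.05, no covariate adjustment, and all 28 per group contributing full data. The last assumption favours the trial, because 28 is the number before attrition. If the allowed loss had already occurred by Day 3, 22 per group would give 62% at d = 0.7. Loss by Day 3 may well be smaller than loss by Day 90, so that is a lower reference point and not a forecast. In the other direction, baseline adjustment would give 77% to 90% for assumed correlations of 0.3 to 0.6. The article does not claim this gain.

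This must be corrected, because a headline power figure tied to the stated target effect is wrong as printed.

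**What to change.** - In Table 1, change the achieved-power column to 98.6%, 84%, 73%, 45% and 12%.
- Replace the sentence after the sensitivity analysis with wording such as: with 28 analysed per group, a two-sided t-test has about 73% power for d = 0.7 and 80% power for d = 0.76. Say that this assumes no loss by Day 3.
- Alternatively, if credit for the baseline adjustment is wanted, state the assumed baseline to Day 3 correlation with its justification, and recompute every row, required n included, on that one basis.
- On either route, bring the required-n cells for 95% power (20, 36 and 46) onto the same basis, so that the first row agrees with the 22 in the text.

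The cost is a correction to one sentence and one table. A stated figure becomes less favourable; no participants are added and the analysis does not change.

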#### Randomization and blinding

2.1.3

A comprehensive randomization procedure was implemented in which an independent third-party researcher utilized the Research Randomizer software^2^ to generate a random sequence of numbers ranging from 1 to 56. Each number was then placed into a correspondingly numbered, sealed, opaque envelope. To maintain allocation concealment, all envelopes were securely stored by designated personnel. Following the identification of the research subjects, the researchers contacted the custodians of the random number envelopes via telephone to inquire about the grouping procedure. The custodians subsequently activated the envelopes in sequential order and organized the subjects accordingly. When the number contained within the envelope is odd, the research participant is allocated to the intervention group; conversely, when the number is even, the participant is assigned to the control group.

Due to the nature of the face-to-face psychological intervention, complete blinding was not feasible for the intervention providers or research subjects. To minimize potential bias, the following blinding procedures will be implemented: (1) Blinding of outcome assessors: Staff responsible for outcome assessment will be kept unaware of group allocation and will have no involvement in the intervention or randomization. (2) Blinding of data analysts: Analysts will remain blinded to group assignment until the final analysis is completed and the database is locked. (3) Procedures to maintain blinding: To safeguard blinding, all study materials will use coded participant IDs without any group indication. The allocation list will be kept by an independent research coordinator not involved in assessment or analysis.

### Intervention

2.2

#### Control group

2.2.1

Participants randomized to the control group will receive standard care, which is strictly limited to informational and procedural support. The components are as follows: (1) During ICU hospitalization. (1) Informational support: Nursing staff will provide a concise introduction to the ICU environment, equipment, and visiting policies. (2) Medical staff will communicate essential information regarding the patient’s clinical status, treatment plan, and progress. (3) Basic care guidance: Family members will be instructed on fundamental, task-oriented nursing skills necessary for patient care (e.g., assisting with rehabilitation exercises, basic daily care) as appropriate. (4) Psychological support: To minimize contamination, control group participants will not receive any proactive, structured, or protocol-driven psychological counseling from the ICU clinical team or study personnel during the 3-day intervention window. This includes, but is not limited to: stress management techniques, relaxation training, cognitive reframing, or any form of psychotherapy. If a family member exhibits signs of significant psychological distress that require clinical attention, the ICU clinical team will follow the hospital’s standard protocol, which typically involves notifying the attending physician and/or initiating a referral to the hospital’s psychiatric liaison service. Such instances will be documented as exceptional clinical events and are not considered routine components of standard care. (2) Post-discharge follow-up. The health guidance and follow-up mentioned will be confined to routine medical advice (e.g., medication management, wound care) and the administration of outcome assessments for this study. It will not include systematic psychological support or counseling components. (3) Documentation of co-interventions. To ensure transparency and enable appropriate statistical adjustment, any instance of substantial psychological support provided to a control group participant outside the study protocol will be systematically documented by the research team using a standardized co-intervention documentation form. The following information will be recorded: type of support, duration, timing, reason/trigger. These data will be monitored throughout the trial by the research team. In the primary analysis, between-group comparisons will be conducted regardless of co-intervention exposure. As a pre-specified sensitivity analysis, we will compare the primary outcomes after excluding participants who received any protocol-prohibited psychological support, to assess the potential impact of such co-interventions on the study results. Additionally, if the frequency of co-interventions differs substantially between groups, this will be addressed in the interpretation of findings.

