
#### Experimental group

2.2.2

The experimental group will receive the SAF-T intervention in addition to the standard care provided to the control group. The SAF-T intervention was developed by the research team following an extensive review of the literature. The team comprises ICU clinicians, specialized ICU nurses, and psychiatrists and psychologists, all of whom possess substantial clinical expertise. The detailed SAF-T intervention script is provided in Table 2. Before the commencement of the formal study, to ensure the standardized implementation of the intervention, a clinical psychotherapist from the intervention development team provided SAF-T training to another researcher in the study team with EMDR learning experience. The training covered the theoretical framework and specific procedures of SAF-T, as well as the instruction of relevant psychological intervention techniques. The training process is monitored by all members of the intervention-constructed team. To ensure the consistency of the SAF-T intervention protocol, the psychological intervention will be delivered by a fixed, dedicated research member. Following each session, the interventionist will complete a session checklist to document adherence to the specific operational procedures. To proactively monitor participant well-being, the interventionist will conduct structured inquiries at the beginning and end of each session using a combination of open-ended and closed-ended questions. Throughout the session, the interventionist will remain vigilant for signs of emotional deterioration, such as crying, agitation, reduced verbal output, or expressions of hopelessness. Should such signs emerge and significantly impede the session’s progress, the intervention will be paused temporarily. The interventionist will then provide support, ensure the participant’s immediate stability, and respectfully inquire about their willingness to continue. If resumption is not feasible, the session will be rescheduled. Furthermore, participants are explicitly informed that they may pause or withdraw from the intervention at any time due to emotional discomfort without any penalty or consequence.

**Table 2 tab2:** SAF-T intervention script.

Component	Description
Objective	To alleviate stress, anxiety, and depression in ICU patients’ family members via SAF-T, empowering them for independent stress management. Skill application is encouraged based on personal relevance, not mandated.

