. Finally, the three standardized scores will be summed to obtain the participant’s psychological distress composite score: 
$\text{CompositeScor}e_{i}=Z_{i,\mathrm{PSS}-10}+Z_{i,\mathrm{GAD}-7}+Z_{i,\mathrm{PHQ}-9}.$
 (2) Primary statistical model. The primary between-group comparison at Day 3 will be performed using an analysis of covariance (ANCOVA), with the Day 3 composite score as the dependent variable, experimental group as the fixed factor, and the baseline composite score as a covariate. Prior to ANCOVA, normality of residuals and homogeneity of regression slopes will be assessed. If the assumptions of ANCOVA are violated, a non-parametric alternative (e.g., Quade’s rank ANCOVA) will be applied. (3) Effect size and validation. To assess the clinical significance of the intervention effect, Cohen’s d effect size will be calculated, with *d* = 0.2 considered a small effect, *d* = 0.5 a medium effect, and *d* = 0.8 a large effect (Bartko et al., 1988). As a validation step, the theoretical standard deviation of the composite score will be computed using the variance sum theorem: 
$SD_{\text{theoretical}}=\sqrt{3+2(r_{12}+r_{13}+r_{23})}$
. where 
$r_{12}$
, 
$r_{13}$
, and 
$r_{23}$
 represent the Pearson correlation coefficients between each pair of the three scales. This theoretical value will be compared with the observed standard deviation to confirm the construct validity of the composite score. (4) Sensitivity analyses. As a sensitivity analysis, a per-protocol (PP) analysis will be conducted to evaluate the robustness of the primary ITT results. Additionally, to assess the potential impact of contamination, we will perform an analysis excluding control group participants who received protocol-prohibited psychological support during the intervention window.

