Additional Analyses: Intra-group changes from baseline to specific time points for normally distributed data will be assessed using paired *t*-tests, or the *Wilcoxon* signed-rank test for non-normally distributed data. And we will assess the sensitivity of the results to potential contamination by conducting exclusion analysis and reclassification analysis on the control group participants who received additional support.

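### The co-intervention form covers control participants only although its frequency is to be compared between groups, and the support that leads to exclusion is not defined consistently

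*Protocol article*

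**What the plan says.** **Recording.** Section 2.2.1 sets up a standardized co-intervention form: "any instance of substantial psychological support provided to a control group participant outside the study protocol will be systematically documented". It captures type, duration, timing and trigger, and its stated purposes include statistical adjustment. Section 2.2.2 gives the SAF-T arm a session checklist, but that records adherence to the intervention procedure, not outside support.

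**Use between arms.** The same paragraph of section 2.2.1 adds: "if the frequency of co-interventions differs substantially between groups, this will be addressed in the interpretation of findings".

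**Exclusion analysis.** It appears in three places:
- Section 2.2.1, as a pre-specified sensitivity analysis: "excluding participants who received any protocol-prohibited psychological support".
- Section 2.6, sensitivity analyses of the primary outcome: "excluding control group participants who received protocol-prohibited psychological support during the intervention window".
- Section 2.6, additional analyses: "conducting exclusion analysis and reclassification analysis on the control group participants who received additional support".

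**Primary analysis.** Section 2.2.1 makes the primary comparison whatever co-interventions were received.

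**The concern.** The plan promises to interpret a difference between arms in a quantity that it collects in one arm. SAF-T participants can also receive outside psychological support, for example a liaison referral. Without the form in that arm, a count of zero there would mean only that nobody was asked to record it. An apparent excess in controls would then reflect who gets the form.

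The second problem is which controls leave the sensitivity analysis. If the class of support is open, the excluded set can be settled after the data are seen. In a group of 28, moving two or three people in or out matters to a secondary estimate. Those who receive support are also plausibly the more distressed, so removing them from one arm changes the comparison even if the support did nothing.

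**Working it through.** **1. Can the form deliver the comparison?** Comparing frequency between arms needs a count and a denominator in each arm. The form gives a count out of 28 controls. No section of the article provides an equivalent count out of the 28 SAF-T participants, so the comparison cannot be made from the data described.

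The nearest substitute is the record of distress-triggered referrals: "Such instances will be documented as exceptional clinical events". The trigger for that route is worded for any family member, so the record may cover both arms. It would capture referrals only, not the wider class of substantial support that the form is meant to capture.

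**2. Do the exclusion wordings agree?**

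| Place | Who | Which support | Window |
|---|---|---|---|
| 2.2.1 | participants | protocol-prohibited | not stated |
| 2.6, primary outcome | controls | protocol-prohibited | intervention window |
| 2.6, additional analyses | controls | additional support | not stated |

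The only prohibition in the article is in section 2.2.1. It applies to controls during the 3-day window, so the first row implies the second and these two reconcile. The third row does not: additional support is wider than prohibited support, has no window, and comes with a reclassification analysis that is not described. The form has its own, different trigger (substantial support outside the protocol). None of the wordings settles whether a clinical referral counts.

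**3. How far could a controls-only exclusion move the estimate?** The plan states no figure to reproduce, and the number excluded, k, is an assumption.

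*Simple arithmetic.* Let the k excluded controls average D standard deviations above the control mean m. The mean of those remaining is [28m − k(m + D)]/(28 − k) = m − kD/(28 − k), so the control mean falls by kD/(28 − k).

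| D (SD) | k = 2 | k = 4 |
|---|---|---|
| 0.5 | 1.0/26 = 0.038 | 2.0/24 = 0.083 |
| 1.0 | 2.0/26 = 0.077 | 4.0/24 = 0.167 |
| 1.5 | 3.0/26 = 0.115 | 6.0/24 = 0.250 |

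*Planned ANCOVA, simulated.* Inputs: 8,000 trials of 28 against 28, no effect of SAF-T or of the support, and baseline to Day 3 correlation r. The k people highest on a trigger correlated 0.7 with the Day 3 score are excluded. A positive value goes against SAF-T.

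| r | Controls only, k = 2 | Controls only, k = 4 | Same rule in both arms |
|---|---|---|---|
| 0.5 | 0.076 | 0.135 | about 0 |
| 0.7 | 0.050 | 0.090 | about 0 |

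The Monte Carlo standard error is below 0.003.

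*With a true effect.* The zero in the last column depends on there being no treatment effect. Take instead a true benefit of 0.7 SD, the target named in section 2.1.2, and a common distress threshold that excludes about 10% of controls. Controls-only exclusion then shifts the estimate by 0.07 to 0.10 SD, and exclusion in both arms by 0.04 to 0.06 SD (r = 0.7 and 0.5 respectively). The two-arm rule removes about 1 − 0.04/0.07 = 43% to 1 − 0.06/0.10 = 40% of the shift. For scale, the sampling SD of the full-sample ANCOVA estimate in the same set-up is about 0.19 to 0.23 SD.

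**The case against.** **A controls-only exclusion is legitimate.** Section 2.6 gives its purpose as gauging contamination, which here means controls receiving psychological support. Excluding in both arms answers a different question and, as shown above, is not a full cure. This stands, and the point is not that the controls-only analysis is wrong.

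**The bias mechanism is assumed.** What is prohibited is proactive or structured counselling; distress-triggered referral is handled separately. Selection of the most distressed is plausible for referrals but is not shown for prohibited counselling. This also stands: the shifts are illustrations. They are below one sampling SD and go against SAF-T, so they would not create a false positive.

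**The between-group sentence promises interpretation, not a test.** True, but interpretation needs data from both arms too.

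**Condensation does not explain the mismatch.** An article may leave detail to a full protocol, but here both the restriction to controls and the comparison between groups are stated outright.

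Two stronger readings are tempting. A reader might infer that there are three irreconcilable exclusion rules; the scope of the prohibition reconciles two of them. A reader might also infer that distressed SAF-T participants have no clinical route, because section 2.2.2 says only "Should such signs emerge and significantly impede the session’s progress, the intervention will be paused temporarily" and goes on to support and rescheduling. The documents do not support that. The route in section 2.2.1 opens with "If a family member exhibits signs of significant psychological distress that require clinical attention", and the SAF-T arm receives the same standard care. What is absent is at most a cross-reference, which a condensed article may leave to the full protocol.

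**Conclusion.** The point holds in two parts. First, section 2.2.1 contradicts itself: recording is confined to controls, yet frequency is to be interpreted between arms. This rests on the text alone. Second, the excluded set is not fixed, because the additional-analyses paragraph of section 2.6 uses a wider class of support than the other two places and adds an undefined reclassification.

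The consequence is limited. A reader might infer that the main result is biased, but the primary Day 3 comparison is made regardless of co-interventions and is unaffected. Only the description of outside support and a sensitivity analysis are touched. For that analysis, about 0.05 to 0.14 SD against SAF-T is a fair illustration for 2 to 4 exclusions. It assumes no true effect, r of 0.5 to 0.7 and a trigger correlation of 0.7. The article gives no expected rate of outside support, so the actual shift could be smaller or larger.

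**What to change.** 1. **Recording (2.2.1).** Complete the existing form in both arms by the same rule, stating that SAF-T itself is not a co-intervention, and describe the frequency by arm. This has to be done prospectively, because one-arm records cannot be reliably repaired afterwards.
2. **One definition (2.2.1 and both places in 2.6).** State the type of support, the 3-day window, and whether a clinical referral counts. Use the same term on the form.
3. **Reclassification (2.6).** Define it or drop it.
4. **Labelling.** Keep the controls-only exclusion if wished, labelled as a contamination analysis, with a note that removing distressed controls can shift it against SAF-T. A two-arm exclusion may be added, with the caveat that it does not fully remove the shift if SAF-T works.

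The cost is a few wording changes and slightly more record-keeping in the SAF-T arm. With 28 per arm the counts will support description only. Randomization, sample size, endpoint and primary model stay as they are.
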